The IMAGINE study aims to investigate the effects of enriching usual geriatric rehabilitation with an adapted MI approach on different outcomes related to functional and clinical impact, persons’ satisfaction during hospitalization and cost-utility. We expect that the IMAGINE study will add a relevant contribution for the implementation of this intervention in older stroke survivors needing rehabilitation. Accordingly, this study should inform practice and policy makers on how to move forward towards shared decision making and shared responsibilities in a vulnerable population such as older stroke survivors [24]. With these aims, several hypothesis have been put forward:
MI, conducted during in-patient geriatric rehabilitation with older stroke survivors will result in an improvement in functional status at 30 days and 3 months, compared to standard geriatric rehabilitation alone.The MI intervention will induce a statistically and clinically significant increase in physical activity during the stay in the geriatric rehabilitation department, and an improvement in physical performance, compared to controls.The increase in physical activity and performance will be dose-correlated with the improvements in functional status.The intervention will result in a more favorable and satisfying experience with care during hospitalization for the participants, caregivers and professionals involved.Participants will increase their self-efficacy.The intervention will be a cost-effective strategy to improve participant outcomes at an acceptable cost (or even with no relevant incremental costs).The intervention will be safe for the stroke survivors. An increased number of adverse events potentially associated to geriatric rehabilitation and exercise will not be observed in the intervention group compared to control group

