### Sample size calculation & statistical analysis

Sample size calculation is based on the results of previous RCTs assessing the effect of geriatric rehabilitation on improvement of the FIM. Accordingly, it is expected that geriatric rehabilitation will induce a 20 points improvement in FIM between admission and discharge [47]. This change has been established as “minimal clinically meaningful” improvement [48]. It is expected that MI plus geriatric rehabilitation will result in a “moderately relevant” clinical improvement in FIM, estimated to be 30 points. That is, MI will induce an additional improvement of 10 points (which corresponds to approximately 10% of total FIM score), compared to the control group. Considering a common standard deviation of 27.9 points in FIM, a 10% of drop-out rate at 30 days, and accepting an alfa risk of 0.05 and a beta risk of 0.2 in a bilateral contrast, we would need to include 136 stroke survivors in each branch (total sample = 272) to detect this improvement as statistically significant. Calculations were obtained using the GRANMO program [49].

Descriptive statistics will be presented for the overall characteristics of the study sample (intervention and control group) as frequencies and percentages for nominal or categorical variables and means and standard deviations for continuous ones. Baseline comparisons between treatment groups will be assessed as t-tests and chi-square tests, to check for potential imbalances in group composition and characteristics.

The effect of MI in the change in total FIM score between baseline and follow up (30 days) will be explored through a longitudinal repeated-measures mixed effects linear model, with the total FIM score as dependent variable, and a 2-level fixed factor accounting for the treatment group (MI or control). The model will adjust for clinically relevant covariates, such as age, gender and the amount of physical activity.

Group analyses will be carried out on an intention-to-treat principle. Missing data will be replaced by multiple imputations, after conducting explorations of the possible missingness mechanisms.

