Cost-utility analysis will be also performed to compare the benefit and costs of a MI programs. Cost-utility will be measured as the ratio between direct costs (workforce time use to deliver the MI intervention and the related training and supervision, supplementary tests, use of other hospital resources, medical visits, readmissions, treatments, ambulatory rehabilitation, etc.) during hospitalization and also post-discharge (at 3 months) and Quality Adjusted Life Years (QALYs). QALYs will be derived using the EQoL-5D before and after the treatment and at 3 months. Therefore, cost-utility will be calculated as the incremental ratio in € for 1 QALYs in the intervention vs. control group [50, 51].

All analyses will be carried out in Stata 15 (StataCorp. 2017. *Stata Statistical Software: Release 15*. College Station, TX: StataCorp LLC).

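### The only cost-utility result named is a € per QALY ratio, which cannot be read alone if costs are equal or fall; the small 3-month QALY difference would also gain precision from baseline EQ-5D

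*Protocol article*

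**What the plan says.** The cost-utility paragraph of the protocol article (Sample size calculation & statistical analysis) first describes cost-utility as a ratio of direct costs to QALYs. It then concludes that "cost-utility will be calculated as the incremental ratio in € for 1 QALYs in the intervention vs. control group". On the denominator it says that "QALYs will be derived using the EQoL-5D before and after the treatment and at 3 months". Two method references are cited and cannot be seen here.

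The hypotheses in the Background expect the intervention to improve outcomes "at an acceptable cost (or even with no relevant incremental costs"). The discussion part of the abstract adds that less post-stroke disability would lower health and social care spending.

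The minimization factors under Randomization and blinding are study site, gender and type of stroke. Covariate adjustment is described for the FIM model only. For QALYs and costs the article neither plans nor excludes it.

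**The concern.** There are two linked difficulties.

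**Summary measure.** A cost/QALY ratio works when the new treatment costs more and gives more benefit. The plan also entertains equal costs and savings. A negative ratio does not show whether MI is better and cheaper or worse and dearer. When costs fall, a larger benefit makes the ratio less negative, so its size does not rank results either.

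**Denominator.** Three months of follow-up yields a small QALY difference. Baseline utility is part of each participant's QALY and probably predicts the later values. Any chance difference at baseline therefore adds noise to a small quantity, which then becomes the denominator of a ratio.

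At stake is whether the trial can support its cost-effectiveness hypothesis, which the Discussion offers as evidence for health policy.

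**Working it through.** **1. The plan's own figure.** The article gives no utility, QALY, cost or threshold figure, so the only one to reproduce is the sample size, which supplies the number per arm. Inputs: "MI will induce an additional improvement of 10 points"; "Considering a common standard deviation of 27.9 points in FIM"; "accepting an alfa risk of 0.05 and a beta risk of 0.2 in a bilateral contrast"; "a 10% of drop-out rate at 30 days".

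- n per arm = 2 × (1.960 + 0.842)² × 27.9² / 10² = 122.2.
- With drop-out: 122.2 / 0.9 = 135.8, so 136. This matches "136 stroke survivors in each branch (total sample = 272").
- About 122 per arm remain for analysis (136 × 0.9 = 122.4).

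**2. The ratio where costs are equal or fall.** ΔC is incremental cost, ΔQ incremental QALYs, λ the threshold in € per QALY. Net monetary benefit is λΔQ − ΔC. The € amounts are illustrative.

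| ΔC (€) | ΔQ | Ratio (€ per QALY) | Net benefit |
|---|---|---|---|
| −500 | +0.01 | −50,000 | 0.01λ + 500 |
| +500 | −0.01 | −50,000 | −(0.01λ + 500) |
| −500 | +0.02 | −25,000 | 0.02λ + 500 |
| −500 | +0.005 | −100,000 | 0.005λ + 500 |

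Rows 1 and 2 are opposite results with the same ratio. Row 3 is better than row 4, but its ratio is less negative. Net benefit orders all four correctly at any positive λ.

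Now take a true ΔC of 0. Assume a cost SD of €5,000, so that SE(ΔC) = 5,000 × √(2/122) = €640. Assume a true ΔQ of 0.0125 with SE 0.006, and independent normal errors. The QALY gain is estimated as positive in about 98% of simulated trials. The estimated ratio nevertheless falls above and below zero about equally often, with a 95% range of roughly −€200,000 to +€200,000 per QALY. With a true ΔQ of 0.02 the range is about ±€77,000; with 0.007 it is about ±€680,000.

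**3. Size of the QALY difference.** Assume EQ-5D at days 0, 30 and 91 and the trapezoid rule, with a year of 365.25 days.

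- Weights in years: day 0, 15/365.25 = 0.0411; day 30, 45.5/365.25 = 0.1246; day 91, 30.5/365.25 = 0.0835.
- The two follow-up weights sum to 0.2081.
- A utility gain of 0.05 at both follow-ups gives 0.05 × 0.2081 = 0.0104 QALY. Gains of 0.03 to 0.10 give 0.006 to 0.021.

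**4. Effect of baseline utility.** Assume utility SD s, the same correlation r between any two visits, and 122 per arm. Central case: s = 0.25, r = 0.5.

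- SE of the chance baseline difference: 0.25 × √(2/122) = 0.0320.
- Slope of QALY on baseline utility: 0.0411 + 0.5 × 0.2081 = 0.1451.
- Shift in ΔQ from a one-SE imbalance: 0.0320 × 0.1451 = 0.0046, or 45% of 0.0104. Of this, only 0.0320 × 0.0411 = 0.0013 comes from the baseline value's own weight. The rest comes from its correlation with later values.
- Over s = 0.20 to 0.30 and r = 0.4 to 0.7 the shift is 0.0032 to 0.0072, or 31% to 69% of 0.0104.

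**5. What adjustment gains.** Per unit s², the QALY variance is (1 − r)Σw² + r(Σw)² = 0.5 × 0.0242 + 0.5 × 0.0621 = 0.0431.

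- Unadjusted SE of ΔQ: 0.0320 × √0.0431 = 0.0067 (0.00665 before rounding).
- R² for baseline: 0.1451² / 0.0431 = 0.488.
- Adjusted SE: 0.00665 × √(1 − 0.488) = 0.0048, about 28% lower.
- At r = 0.4, R² = 0.393 and the reduction is 22%. At r = 0.7, R² = 0.688 and it is 44%.
- Chance that a true gain of 0.0104 is estimated as a loss in the central case: Φ(−0.0104/0.00665) = 5.9% unadjusted, Φ(−0.0104/0.00476) = 1.4% adjusted.

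**The case against.** The strongest reply is that silence is being read as a decision. This is a condensed article, and adjustment, bootstrap intervals and thresholds are commonly left to a fuller protocol or health-economic plan. An incremental ratio can also be built from adjusted components. This stands. A reader might infer that the article rules out baseline adjustment, but it does not, and the absence of such detail is not itself a fault. What the article does state is the summary measure, and that measure is a ratio.

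A second reply is that the main expectation is better outcomes at an acceptable positive cost, where a ratio is interpretable, and that zero extra cost is only a parenthetical alternative. A reader might infer that the ratio breaks down there. It does not: with a QALY gain and no cost difference it is defined and equals about zero. What remains is a difficulty of interpretation and of its interval when it is reported alone.

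Third, anyone who computes the ratio has both components, and their signs settle the ambiguity. That is correct, and it is a reason to name the components as results.

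Fourth, a reader might infer that unadjusted QALYs are biased, or that an ordinary imbalance would reverse the effect. Neither is supported. Under random allocation the unadjusted difference is unbiased, and the baseline comparisons planned in the article could reveal an imbalance. Cancelling a 0.0104 gain by baseline imbalance alone needs 0.0104 / 0.0046 = 2.2 standard errors in the central case, roughly a 1% event in that direction, and about 1.45 at the top of the assumed range.

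**Conclusion.** The point holds as a minor one on a secondary analysis. The mismatch between the named ratio and the equal-cost or lower-cost results that the article contemplates can be seen in the document itself and depends on no assumed figure. The precision argument does rest on assumptions: the utility SD, the correlation, the visit days, the cost SD and the size of the utility gain are not in the article. A larger true gain makes the imbalance relatively smaller; at 0.10 utility the central share halves to about 22%. The percentage cut in standard error does not depend on the utility SD or the number per arm, only on the correlation and the visit timing. The FIM analysis and the 136 per arm are untouched.

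**What to change.** Estimate incremental QALYs by regression on arm, with baseline EQ-5D utility and the minimization factors (site, gender, stroke type) as covariates. If an unseen plan already does this, a sentence confirming it is enough. Report incremental costs, incremental QALYs and incremental net monetary benefit at € per QALY thresholds stated in advance. Give intervals from a bootstrap that resamples each participant's cost and QALY together. Keep the ratio as a secondary summary.

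The cost is a little more analysis work and about two sentences of plan text. Baseline EQ-5D is already collected, so there is no added burden on participants. The one real commitment is that thresholds must be chosen before the results are known.

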### Legal and ethical aspects

The protocol and the template informed consent forms has been approved by the Ethics Committee on Animal and Human Research (CEEAH) of the Universitat Autònoma de Barcelona (reference number CEEAH 3715). The rest of the participating centers’ Ethics Committees ratified these premises. At the beginning of the project, an advisory board will be created including stroke survivors’ and caregivers’ representatives (from dedicated Associations or from the participating institutions), health and social care professionals and policymakers, which will meet periodically with the research team. The commission of this board will be to: 1) support and give feedback about the refinement of the study and intervention design; 2) promote constant feedback on project progress and help to overcome potential barriers; 3) foster communication, dissemination and knowledge translation.

Prior to any assessment and intervention, all participants in the study granted written and verbal informed consent.

All study-related information will be stored securely at the reference center Server. All participant information will be stored in locked file cabinets in areas with limited access. All reports, data collection, process, and administrative forms will be identified by a coded ID number only to maintain participant confidentiality. All records that contain names or other personal identifiers, such as informed consent forms, will be stored separately from study records identified by code number. All local databases will be secured with password-protected access systems. Forms, lists, logbooks, appointment books, and any other listings that link participant ID numbers to other identifying information will be stored in a separate, locked file in an area with limited access.

The coordinator of each intervention site will be given access to the cleaned data sets, housed on the file transfer protocol site created for the study, and all data sets will be password protected. Project Principal Investigators will have direct access to their own site’s data sets, and will have access to other sites data by request. To ensure confidentiality, data shared with project team members will be completely anonymized without any identifying participant information.

The feasibility and scientific quality of the trial has been peer-reviewed and approved by the Principal Investigators and Research and Development team. The trial protocol will permit its reporting in line with the Consolidated Standards of Reporting Trials (CONSORT) guidelines [26]. The Standard Protocol Items: Recommendations for Interventional Trials (SPIRIT) checklist [52, 53], and the Template for intervention description and replication (TIDieR) checklist [54] are both provided as additional files 1 and 2.

## Results

Final results are expected by end of 2020. See flow chart (Fig. 3).

**Fig. 3 Fig3:**
[figure not shown]
Flow chart

## Discussion

This project is expected to provide new evidence on the impact of MI on older stroke survivors, increasing the understanding on the implementation of a non-pharmacological intervention based on a person-centered approach, and assessing its impacts on objective outcomes. The project will be performed from a “triple aim” viewpoint (healthcare, efficiency and person-centered outcomes and experiences), through multi quantitative and qualitative methods. Accordingly, the IMAGINE study will develop a new area of research with an innovative approach: empowering older stroke survivors that are in vulnerable conditions, and building their rehabilitation process with them rather than only for them. Thus, it changes the person’s perspective from his/her limitations to his/her strengths. In the same line, this study focuses on a novel approach by fostering residual capacities based on personal goals instead of “treating disability”, in line with novel frameworks [10, 55]. The MI approach can easily be part of professional training or configure novel specialty training for healthcare professionals involved in rehabilitation services, providing a unique opportunity of scaling up the intervention. The focus on person centered care is expected to increase person satisfaction, which will be assessed by exploring the experiences of the stroke survivors and professionals involved. In addition, the trial is based on objective outcomes that are relevant for older stroke survivors, since mobility and physical function limitations are a major barrier for quality of life. We will also assess other aspects such as well-being or self-efficacy, as a health resource with major influence on quality of life and with potential to explain the mechanisms of impact of the MI intervention.

Regarding stroke survivors, MI has been used mainly in chronic stages in order to promote and maintain pharmacological treatment and lifestyle changes [32, 56, 57]. Recently, two research groups have described a possible association between the early use of MI, functional and mood improvement and a reduction of mortality [58, 59]. However, as none of these studies focused on older adults, the evidence of its use during the subacute phase of stroke in older adults is scarce [60]. Similarly, English et al. [32] assessed the feasibility of MI in a small sample (*N* = 35) of stroke survivors (> 6 months) in the community. They also assessed the impact on physical activity, as the reduction of sitting time measured using accelerometers. The intervention was found feasible and safe but the observed sitting time reduction was not significantly different from the control group. Recent studies on frail older adults with mobility limitations from the community have confirmed safety and showed potential cost-effectiveness of a rehabilitative person-centered approach [23]. These results are in line with other studies that suggest cost-effectiveness [23, 61], and cost-utility [62, 63] of MI used to promote changes in lifestyle, in different settings and populations. However, such studies have not been carried out with stroke survivors.

Potential critical aspects and risks might be an insufficient sample size or important attrition; although in case of need, other geriatric rehabilitation centers of the Catalan healthcare network (Catsalut) could be included. Strengths of the study are the three intervention sites, referent centers for geriatric stroke rehabilitation in Catalonia, who have also previously shown their recruitment capability. Moreover, our previous MI pilot [27] showed high acceptance of the intervention, which should reduce the risk of dropouts. Although in a non-pharmacologic trial it is almost impossible to blind participants and professionals delivering the intervention, procedures have been set to guarantee as much as possible blinding outcome assessors.

This project has the potential to directly change the decision making process in the rehabilitation of older stroke survivors. As almost half of stroke survivor’s experience relevant residual disability, with stroke being the main cause of disability in Western countries [2], new rehabilitation and recovery strategies are needed and will have a high impact for the society. Likewise, the knowledge gained by this project, including the intervention and its effects also in terms of costs, should inform current health care policies at national and international level on how to enhance established rehabilitation programs with an empowering approach, thus taking a major profit of currently limited economic and human resources.

## Data Availability

Data sharing is not applicable to this article as no datasets were generated or analysed for this study protocol.

## Abbreviations

FIM: Functional Independence Measure
ICF: International Classification of Functioning, Disability and Health
MI: Motivational interviewing
MITI: Motivational Interviewing Treatment Integrity Code
m-RS: Modified-Rankin Scale
NIHSS: National Institute of Health Stroke Severity
QALY: Quality Adjusted Life Years
